### Outcome measurements

Primary and secondary efficacy outcomes were measured once pre-treatment and once post-treatment for a total of two times.

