### Sample size

The sample size was determined based on the sole primary endpoint (CK-MB). Based on previous reports of CK-MB changes in unstable angina patients (15), we conservatively assumed a standardized effect size of d = 0.50 (medium effect). With two-sided α = 0.05% and 80% power, the required sample size for a two-sample t-test was 63 per group. Because the primary analysis will use ANCOVA with baseline adjustment, the sample size was reduced by a factor of (1–R²), assuming R² = 0.40, yielding approximately 38 per group. After considering a 20% attrition rate, the final target enrollment was 50 per group, 100 in total. Calculations were performed using G*Power v3.1.9.7

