### Statistical analysis

Statistical analyses will be performed using R software (version 4.3.2). All tests will be two-sided with α=0.05. The primary outcome (Day-7 CK-MB, baseline-adjusted) will be analyzed by ANCOVA, with treatment group as a fixed factor and baseline CK-MB as a covariate. Major concomitant medications will also be included as covariates, specifically: (1) dual antiplatelet therapy; (2) statins; (3) β-blockers; and (4) ACEI/ARB. For each class, exposure during the 7-day intervention window will be coded “Yes” if the drug was taken on ≥80% of on-study days (≥6/7 days), otherwise “No”. The treatment effect will be reported as the adjusted mean difference with 95% CI. Secondary outcomes will be analyzed using ANCOVA or appropriate parametric/non-parametric tests with the same covariates. *P*-values for these outcomes will be nominal without multiplicity adjustment and interpreted as exploratory. Safety outcomes will be summarized descriptively by incidence (*n*, %) and compared between groups using χ² or Fisher's exact test, as appropriate.

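### Secondary outcomes are given the primary model's covariates, whose only baseline value is CK-MB; the plan should name each outcome's own baseline instead

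*Protocol article*

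**What the plan says.** The Statistical analysis section describes the primary ANCOVA "with treatment group as a fixed factor and baseline CK-MB as a covariate". It adds four Yes/No medication covariates: dual antiplatelet therapy, statins, β-blockers and ACEI/ARB. For everything else it says: "Secondary outcomes will be analyzed using ANCOVA or appropriate parametric/non-parametric tests with the same covariates".

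The Outcome measurements section shows that the own baselines exist: "Primary and secondary efficacy outcomes were measured once pre-treatment and once post-treatment for a total of two times". The Secondary outcomes section defines the biomarkers (cTnT, NT-proBNP, hs-CRP, IL-6, MMP-9, VEGF, HMGB1) as changes from baseline to Day 7 and lists changes in angina frequency and severity. The Statistical analysis section makes the secondary p-values nominal and exploratory.

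**The concern.** The covariate list that the secondary outcomes inherit contains one baseline value, and it belongs to a different variable. An analyst who codes the sentence as printed would regress the change in hs-CRP on treatment, baseline CK-MB and medications, and leave baseline hs-CRP out.

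Defining the outcome as a change does not make the own baseline redundant. Unless the baseline and Day-7 values are perfectly correlated, the change stays negatively correlated with the baseline. An unadjusted change score is therefore noisier than own-baseline ANCOVA and over-corrects for any chance difference between the arms at baseline.

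The plan relies on this very gain for CK-MB: its sample size is cut by 40% because the baseline is in the model. At stake are the estimates and intervals for the markers that carry the residual-inflammation part of the hypothesis in the Introduction. Those results are also meant to inform later confirmatory trials.

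**Working it through.** **1. The plan's own figure.** The Sample size section states "With two-sided α = 0.05% and 80% power, the required sample size for a two-sample t-test was 63 per group", with "we conservatively assumed a standardized effect size of d = 0.50 (medium effect". The normal-approximation formula for d = 0.50, two-sided α = 0.05 and 80% power gives 63 per group (64 by the exact t calculation). The percent sign after 0.05 cannot be meant literally: α = 0.0005 would need 150 per group, and the Statistical analysis section says "All tests will be two-sided with α=0.05". I use 0.05. Next comes "the sample size was reduced by a factor of (1–R²), assuming R² = 0.40, yielding approximately 38 per group": 63 × (1 − 0.40) = 37.8, so 38. Then "After considering a 20% attrition rate, the final target enrollment was 50 per group, 100 in total": 38 / 0.80 = 47.5, so 48, against 50 stated. The plan's figure is reproduced to within 2 per group. Evaluable patients: 50 × 0.80 = 40 per arm.

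**2. Assumptions for a secondary marker.** The article gives no effect size, SD or correlation for any secondary outcome. For illustration I carry over d = 0.50 (in Day-7 SD units) and R² = 0.40 from CK-MB, so the correlation of a marker's baseline with its Day-7 value is r = √0.40 = 0.632. I assume equal variances at the two times and a normal linear model, and ignore the medication covariates. Let k be the correlation of baseline CK-MB with the marker's own baseline. It is unknown, so I vary it from 0 to 0.6. CK-MB is assumed to relate to the Day-7 value only through that baseline.

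**3. Residual variance, relative to the Day-7 variance.**
- Own-baseline ANCOVA: 1 − r² = 0.600
- Change score, no own baseline: 2(1 − r) = 0.735
- Change score plus baseline CK-MB: 2(1 − r) − k²(1 − r)² = 0.723 at k = 0.3, 0.686 at k = 0.6
- Raw Day-7 value plus baseline CK-MB: 1 − (k·r)² = 1.000 at k = 0, 0.964 at k = 0.3, 0.856 at k = 0.6

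The change score against own-baseline ANCOVA has a variance ratio of 2/(1 + r) = 1.225, so its confidence interval is √1.225 = 1.107 times as wide, about 11%.

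**4. Power** (non-central t, 40 per arm, standardised effect 0.50/√variance).

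| Analysis at R² = 0.40 | Power | Loss (points) |
|---|---|---|
| Own-baseline ANCOVA | 81.3% | – |
| Change score, no own baseline | 73.1% | 8.2 |
| Change score + CK-MB, k = 0.3 | 73.8% | 7.5 |
| Change score + CK-MB, k = 0.6 | 76.0% | 5.3 |
| Raw Day-7 + CK-MB, k = 0 | 59.8% | 21.5 |
| Raw Day-7 + CK-MB, k = 0.3 | 61.4% | 20.0 |
| Raw Day-7 + CK-MB, k = 0.6 | 66.5% | 14.8 |

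**5. Sensitivity to R²** (own-baseline ANCOVA against change score without it).

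| R² | ANCOVA | Change score | Loss (points) |
|---|---|---|---|
| 0.20 | 69.5% | 55.6% | 13.9 |
| 0.30 | 75.1% | 64.1% | 11.0 |
| 0.40 | 81.3% | 73.1% | 8.2 |
| 0.50 | 87.8% | 82.3% | 5.5 |
| 0.60 | 93.7% | 90.8% | 2.9 |
| 0.70 | 98.1% | 97.2% | 0.9 |

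If all 50 per arm were evaluable, the loss at R² = 0.40 would be 6.9 points (89.2% against 82.3%).

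**6. Chance imbalance.** The SD of the baseline difference between arms is √(2/40) = 0.22 SD. A change-score estimate carries (r − 1) = −0.37 times that difference and a raw Day-7 estimate carries +0.63 times. A 0.2 SD imbalance therefore moves a change-score estimate by 0.37 × 0.2 = 0.07 SD, against an assumed effect of 0.50 SD.

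**The case against.** The strongest reply is that the sentence is shorthand. The article describes its method as baseline-adjusted ANCOVA, and the medication list is the covariate text nearest to the phrase. The same covariates could thus mean the outcome's baseline plus the medications. This is also a condensed article, and a fuller protocol or analysis plan, not shown, may spell out the models. That much stands: the article does not establish that the trial will omit the own baselines. It does not remove the point, because the article defines a covariate set whose only baseline is CK-MB and two analysts could fit different models from it.

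A reader might infer a fixed power loss of about 8 points. The article does not support that. It plans d and R² for CK-MB alone, powers no secondary outcome and allows non-parametric tests, to which the calculation does not apply.

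A reader might also infer that the secondary estimates would be biased. Under randomisation they are not biased on average. The imbalance is chance, and the change score already uses each marker's own baseline and removes part of it.

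Nor may one take for granted that baseline CK-MB says little about the other markers. The article gives no such correlation, and its Discussion groups cTnT with CK-MB as markers of myocardial injury. That is why k is varied above; even at k = 0.6 the own baseline does better.

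**Conclusion.** The point holds as a defect of wording with a modest statistical consequence. If followed literally, the sentence gives each secondary outcome a less precise model than the collected data allow and leaves part of any chance baseline difference in the estimate. With values borrowed from CK-MB (d = 0.50, R² = 0.40, 40 evaluable per arm), power falls from about 81% to 73% for a change score. Across R² from 0.20 to 0.70 that loss runs from about 14 points to 1. If raw Day-7 values were analysed, the loss at R² = 0.40 would be about 15 to 21 points, depending on how far baseline CK-MB stands in for the missing baseline. These figures illustrate scale; they are not properties of the plan.

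The primary CK-MB analysis is unaffected, because it already has its own baseline. The exploratory status of the secondary outcomes limits the importance of the point, but the change is still worth making because it costs almost nothing.

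**What to change.** Keep the sentence on secondary outcomes and add to its closing reference to the covariates: *except that baseline CK-MB is replaced by the baseline value of the outcome being analysed*. If own-baseline adjustment was always intended, the same clause records it.

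Confine the change to that swap. It should not remove the four medication covariates from the secondary models or the option of another test for non-normal or count outcomes such as angina attack frequency; those are separate matters.

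The cost is one clause, to be settled before unblinding. No new visits, samples or patients are needed. A patient without a baseline value for a given marker has to be handled for that marker, but the change-from-baseline definition already requires this.

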**Conclusion:**

This exploratory study will evaluate the efficacy and safety of XST in reducing myocardial injury and residual risk in UA patients, providing evidence for future large-scale confirmatory trials.

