We previous conducted a multicenter, clinical trail (Registration No. ChiCTR1800015911) in provinces/municipalities in China from 2020 to 2022 (12). The aim of this study was to evaluate the efficacy and safety of XST in combination with dual antiplatelet therapy on MACE in patients with UA. A total of 1229 UA patients from 16 provincial administrative regions in China were enrolled in the study. The results of the median follow-up of 6 months showed that the incidence of MACE was reduced by 46.7% in the XST group compared with the control group, with time to MACE onset prolonged (27.88 vs. 19.60 days), and no significant difference in major bleeding events between the two groups. Although this trial confirmed that XST significantly reduced MACE risk, the underlying mechanisms remained unclear. Based on this, we designed the present study to test the hypothesis that XST may exert cardiovascular protection by attenuating myocardial injury and ameliorating residual inflammatory risk, as assessed by biomarkers including CK-MB, cTnT, NT-proBNP, hs-CRP, IL-6, MMP-9, VEGF, and HMGB1. This trial aims to elucidate the pleiotropic cardioprotective mechanisms of XST and provide evidence for its integration into precision secondary prevention strategies.

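### Safety is compared between groups only by a χ² or Fisher test, which says little about harm at 50 per arm; a risk difference with a 95% CI would say more at almost no cost

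*Protocol article*

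**What the plan says.** The abstract's Conclusion makes safety one of two aims: "This exploratory study will evaluate the efficacy and safety of XST in reducing myocardial injury and residual risk in UA patients". The method is in Statistical analysis: "Safety outcomes will be summarized descriptively by incidence (*n*, %) and compared between groups using χ² or Fisher's exact test, as appropriate". The level is set at the start of the same section: "All tests will be two-sided with α=0.05".

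That section handles the other outcomes differently. For the primary outcome, "The treatment effect will be reported as the adjusted mean difference with 95% CI". P-values for the secondary outcomes are to be nominal and read as exploratory. Safety gets neither an interval nor that caution.

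Under Sample size, "the final target enrollment was 50 per group, 100 in total", and that section derives the number from CK-MB only. The safety set contains everyone who received at least one dose, so up to 50 per arm.

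**The concern.** A trial sized on a biomarker has no designed power for adverse events. If the only comparative safety result is a p-value, it will often be non-significant whether or not the 500 mg arm has a moderate excess of events, so it does not separate the two situations. A risk difference with an interval states directly which excess the data still allow.

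Bleeding is the natural example on the article's own terms. Dual antiplatelet therapy is background treatment, patients at increased bleeding risk are excluded, and the Discussion cites inhibition of platelet aggregation by XST. The Introduction reports the earlier 1229-patient trial's bleeding result as "no significant difference in major bleeding events between the two groups". The same phrase from a trial of 100 would carry much less information, and the present results are meant to inform confirmatory trials.

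**Working it through.** **Plan's own sample size.** Inputs from Sample size: d = 0.50, 80% power, R² = 0.40, 20% attrition. I take two-sided α as 0.05. The article prints 0.05% there, but its figures fit only 0.05, the level given in Statistical analysis.
- Two-sample n per group: 2 × (1.96 + 0.842)² / 0.50² = 62.8, so 63.
- ANCOVA reduction: 63 × (1 − 0.40) = 37.8, so 38.
- Attrition: 38 / (1 − 0.20) = 47.5, so 48, against 50 stated.

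The figure reproduces to within 2 per group, and no safety rate or margin enters it.

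**Power of the planned safety test.** Inputs: n = 50 per arm and two-sided 0.05, from the article. Event rates are assumptions, because the article gives none. Power is the sum, over all pairs of counts (i, j) that the test calls significant, of Bin(i; 50, p₁) × Bin(j; 50, p₂). The miss rate is 1 − power.

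| Control vs 500 mg (assumed) | Fisher miss rate | Uncorrected χ² miss rate |
|---|---|---|
| 5% vs 10% | 94% | 86% |
| 5% vs 15% | 76% | 61% |
| 5% vs 20% | 49% | 34% |
| 2% vs 10% | 81% | 62% |
| 10% vs 20% | 81% | 70% |

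Fisher first reaches 80% power at 18.5%, 21%, 26.5% and 34.5% for control rates of 1%, 2%, 5% and 10%. These are excesses of 17.5, 19, 21.5 and 24.5 points. Which column applies depends on how the choice of test is made. With few events it is usually Fisher.

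**What an interval adds.** Newcombe's interval combines the Wilson limits (l, u) of the two arms. With d = p₁ − p₂, the lower limit is d − √[(p₁ − l₁)² + (u₂ − p₂)²] and the upper limit is d + √[(u₁ − p₁)² + (p₂ − l₂)²].
- 5/50 vs 0/50: Fisher p = 0.056. The Wilson limits are 4.35% to 21.36% and 0% to 7.13%. The lower limit is 0.100 − √(0.0565² + 0.0713²) = 0.009 and the upper is 0.100 + 0.1136 = 0.214. The interval is +0.9 to +21.4 points.
- 5/50 vs 2/50: Fisher p = 0.44; the interval is −5.0 to +17.7 points.
- 0/50 in one arm: the exact two-sided 95% upper limit is 1 − 0.025^(1/50) = 7.1%.

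In the first two cases a report confined to the test would read as no significant difference, although the intervals reach excesses of about 18 to 21 points.

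**The case against.** The strongest reply has four parts.

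First, the article sets no safety hypothesis, margin or decision rule. The phrase about no significant difference describes another trial. This stands. A reader might infer that the plan will treat p > 0.05 as proof of safety, but nothing in the article says so.

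Second, description comes first: "Safety outcomes will be summarized descriptively by incidence". With n and % per arm, any reader can compute an interval. This also stands, so the comparison is not closed off. It does not change which comparative result the authors have chosen to produce.

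Third, the trial calls itself small and exploratory, low power for harms comes with that, and an interval adds no ability to detect them. That is correct, and no more patients are asked for. The gain is that the uncertainty is shown.

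Fourth, interval methods are detail that a condensed article may leave to a fuller document. This holds in part, and intervals may already be planned there. But the article does more than stay silent: it names a significance test as the between-group method, and a better one is available.

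It is also tempting to say that the trial would miss most relevant harms. The article does not support that. It gives no event rates, and a large excess such as 5% versus 26.5% would be found about 80% of the time.

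**Conclusion.** The point holds as a modest improvement to a stated method. At 50 per arm, under assumed rates, Fisher's test misses a 5-point excess over 5% nearly always and a 10-point excess about three times in four. A 15-point excess is missed about half the time. The χ² test does somewhat better (86%, 61% and 34% missed) without changing the picture. A non-significant result therefore says little about moderate harm. The size depends on the assumed rates and on all 50 patients per arm being dosed; smaller arms would make it worse. The plan contains no false safety conclusion and no contradiction on this point.

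**What to change.** In Statistical analysis, make the between-group risk difference with its 95% CI (for example Newcombe) the comparative safety output. Apply it to adverse events, serious adverse events, bleeding and clinically significant laboratory abnormalities. Add the exact 95% upper limit of the incidence in any arm with no events. Keep χ² or Fisher p-values only as nominal and descriptive, in line with the secondary outcomes. Add one sentence saying that a non-significant difference will not be read as evidence of safety. If the full protocol or SAP already plans such intervals, it is enough to align the article's sentence.

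The cost is a few sentences and a few lines of R, with no new data, patients or procedures. The downside is that the intervals will be wide and the safety statement will look less reassuring.

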### Exclusion criteria

Patients meeting any of the following conditions will be excluded from this study:
1.Severe cardiovascular conditions: (1) New York Heart Association (NYHA) class IV heart failure; (2) UA with high short-term risk stratification; (3) Uncontrolled grade III hypertension (systolic blood pressure ≥180 mm Hg and/or diastolic blood pressure ≥110 mm Hg).2.Increased risk of bleeding: History of major organ bleeding within the past six months; Thrombocytopenia or coagulation abnormalities; Active bleeding within the past month.3.Severe comorbidities or contraindications: Abnormal liver or renal function tests; Pregnant or breastfeeding women, or those planning pregnancy during the study period; Patients with malignant tumors, severe psychiatric disorders, or other serious systemic diseases affecting survival.4.Patients who refused to participate in this study.

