### Safety assessment

An adverse event (AE) refers to any unintended medical occurrence observed during the trial, regardless of its relationship to the study intervention. Throughout the study period, researchers will monitor vital signs (e.g., blood pressure, heart rate); Perform blood tests, urinalysis, and assess renal/liver function (at baseline and post-treatment). Document any clinically significant abnormalities or AEs identified during the trial.

If an AE occurs, the research team will clinically evaluate whether to pause participant involvement, initiate diagnostic procedures, or adjust treatment plans. For severe AEs (SAEs), immediate medical intervention will be prioritized to ensure participant safety. All SAEs must be reported to the institutional ethics committee within 24 h of identification.

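### Continuous laboratory safety values are measured at baseline and post-treatment, but the only stated safety analysis is incidence with χ² or Fisher, which is insensitive to small or moderate shifts of a whole arm

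*Protocol article*

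**What the plan says.** All quotes are from the protocol article.

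- **Statistical analysis.** One sentence covers safety: "Safety outcomes will be summarized descriptively by incidence" (n, %), with the groups compared by χ² or Fisher's exact test. It does not name laboratory values or vital signs, and it mentions no change from baseline or shift summary.
- **Safety assessment, laboratory.** Researchers will "Perform blood tests, urinalysis, and assess renal/liver function (at baseline and post-treatment").
- **Safety assessment, vital signs.** These follow a different schedule: "Throughout the study period, researchers will monitor vital signs (e.g., blood pressure, heart rate").
- **Safety assessment, recording.** The section then asks researchers to "Document any clinically significant abnormalities or AEs identified during the trial".
- **Exclusion criteria.** Patients are excluded for "Abnormal liver or renal function tests" and for "Thrombocytopenia or coagulation abnormalities". For blood pressure, only uncontrolled grade III hypertension excludes.
- **Efficacy biomarkers.** These are also measured once before and once after treatment. CK-MB gets ANCOVA adjusted for its own baseline. The secondary outcomes get ANCOVA or suitable parametric or non-parametric tests.

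**The concern.** Most blood tests and renal or liver function tests give continuous values, and here each patient has one before and one after treatment. To report such a value as an incidence, it must first be reduced to abnormal or not abnormal. That step drops how far the value moved and where it started.

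The loss matters more for liver and renal tests because patients who are abnormal at entry are excluded. Exposure lasts 7 days, so few patients may be expected to cross a limit even if the whole arm has moved towards it.

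Safety is a stated aim in the abstract's conclusion, and the results are meant to inform larger confirmatory trials. If the text is followed as written, a moderate rise in creatinine or transaminases across the 500 mg arm could appear as a few extra abnormal results and a non-significant test. The data that would show the shift more clearly are already being collected.

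**Working it through.** **The plan's own figures.** No safety figure is stated. The arm size comes from the Sample size section: 63 × (1 − 0.40) = 37.8, rounded to 38, and 38 / 0.80 = 47.5, rounded to 48, against 50 stated. I use 50 per arm, and 50 × 0.80 = 40 per arm if the 20% attrition occurs. The level is two-sided 0.05, from the Statistical analysis section.

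**Assumptions not in the documents.** The laboratory value is normal, after a log transformation if needed. The whole 500 mg arm shifts by 0.5 SD. The share of controls beyond the limit at Day 7 is 2.5%, 5% or 10%. Baseline explains R² = 0, 0.3 or 0.5 of the post-treatment variance.

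**Step 1: abnormal rates.** If a share p0 of controls exceeds the limit, the limit lies at z = Φ⁻¹(1 − p0), and the shifted arm exceeds it with probability p1 = 1 − Φ(z − 0.5).

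- p0 = 2.5%: z = 1.960, p1 = 1 − Φ(1.460) = 7.2%
- p0 = 5%: z = 1.645, p1 = 1 − Φ(1.145) = 12.6%
- p0 = 10%: z = 1.282, p1 = 1 − Φ(0.782) = 21.7%

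**Step 2: Fisher power.** This is the sum of the two binomial probabilities over all tables with Fisher p ≤ 0.05.

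| Control vs 500 mg arm | 50 per arm | 40 per arm |
|---|---|---|
| 2.5% vs 7.2% | 5% | 3% |
| 5% vs 12.6% | 14% | 10% |
| 10% vs 21.7% | 26% | 21% |

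With no abnormal control at 50 per arm, 5 abnormal results in the 500 mg arm give p = 0.056. Six are needed to fall below 0.05.

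**Step 3: the same shift, baseline-adjusted.** Two-sample t power with effect 0.5 / √(1 − R²).

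| R² | Effect | 50 per arm | 40 per arm |
|---|---|---|---|
| 0 | 0.500 | 70% | 60% |
| 0.3 | 0.598 | 84% | 75% |
| 0.5 | 0.707 | 94% | 88% |

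At R² = 0.40, the value that the plan assumes for CK-MB, power is 89% with 50 per arm and 81% with 40.

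**Step 4: entry selection modelled directly.** Step 2 does not model the exclusion of abnormal baselines. Here the baseline is cut off at the upper limit (+1.96 SD), and the correlation of baseline with post-treatment value is 0.5 to 0.8. With 50 per arm:

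| Shift | Abnormal, control vs 500 mg arm | Fisher | Baseline-adjusted |
|---|---|---|---|
| 0.3 SD | about 1.5–2% vs 3.5–4% | below 1% | 40–70% |
| 0.5 SD | about 1.5–2% vs 5.5–6.5% | 3–4% | 82–98% |
| 0.8 SD | about 1.5–2% vs 10–11% | about 26% | above 98% |
| 1.0 SD | about 1.5–2% vs 15–16% | 55–58% | above 99% |

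At 40 per arm and 1.0 SD, Fisher has about 40%.

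**Step 5: harm in a subset.** Baseline is cut off as in step 4, with correlation 0.6, a 4 SD rise in only some patients of the 500 mg arm, and 50 per arm. By simulation, with 15% affected, Fisher has about 60% and ANCOVA about 65%. With 20% affected, both have about 84%.

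**The case against.** **The article is condensed.** Laboratory summaries are often left to the full protocol or SAP, and the safety sentence does not name laboratory values. A reader might infer that continuous values will never be analysed. The documents do not support that, because an SAP may add such summaries. What stands against the objection is that the article does not leave the matter open. It names the summary and the tests for safety outcomes, and that rule has no place for a continuous value.

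**The safety outcome described is an event.** The instruction to document clinically significant abnormalities and adverse events fits incidence with χ²/Fisher. This stands, and that analysis should stay for those outcomes. It does not use the paired laboratory values.

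**Vital signs are different.** They are monitored throughout, not as a stated before-and-after pair, and patients are not selected for normal blood pressure. The selection argument therefore covers liver and renal tests, and by a similar exclusion platelets and coagulation, but not vital signs.

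**Selection cuts both ways.** Patients just below a limit remain eligible. Excluding abnormal baselines also makes each later liver or renal abnormality treatment-emergent, so single events are easier to interpret. This stands, but it does not restore sensitivity to a shift within the normal range.

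**A drug effect need not be hidden.** A reader might infer that any laboratory effect would be almost invisible. Steps 4 and 5 show otherwise for large shifts and for harm in a subset.

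**Testing everything invites false signals.** With 20 independent parameters at 0.05, the chance of at least one false signal is 1 − 0.95²⁰ = 64%. This stands, and it is the reason to ask for estimates and not tests.

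**Conclusion.** The point holds, limited to continuous laboratory values and to small or moderate shifts of a whole arm. As written, the safety rule dichotomises these values and drops their size and baseline. For a uniform 0.5 SD shift at 50 per arm, Fisher has about 5–26% power against about 70–94% for a baseline-adjusted comparison. At 40 per arm the ranges are 3–21% and 60–88%. Modelling normal baselines explicitly widens the gap.

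These figures rest on an assumed normal scale, position of the limit, shift and baseline correlation, none of which the protocol gives for laboratory values. The direction was the same in every whole-arm scenario tried, and in the subset scenarios the baseline-adjusted analysis was no worse than Fisher. No decision rule in the trial depends on a safety test, so this is a worthwhile improvement to the plan and not a threat to its primary conclusion.

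**What to change.** In the Statistical analysis section, limit incidence (n, %) with χ² or Fisher to adverse events, clinically significant abnormalities and other categorical safety results. Then add wording such as:

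*On the Safety Set, each continuous laboratory value will be summarised by arm at baseline, at post-treatment and as change. The between-arm difference adjusted for the baseline value (or ratio, if the value is skewed) will be given with its 95% CI and read as an estimate, not a test. Counts of shifts from normal to abnormal will be tabulated. Vital signs will be summarised in the same way from their baseline and end-of-treatment readings.*

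No new patients, visits or blood samples are needed. The cost is one more set of safety tables and several intervals without multiplicity adjustment. The plan already reads its secondary outcomes as exploratory without such adjustment.
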